## Abstract

Mobile crisis services for people experiencing distress related to mental health or substance use are expanding rapidly across the US, yet there is little evidence to support these specific models of care. These new programs present a unique opportunity to expand the literature by utilizing implementation science methods to inform the future design of crisis systems. This mixed methods study will examine the effectiveness and acceptability of the Street Crisis Response Team (SCRT), a new 911-dispatched multidisciplinary mobile crisis intervention piloted in San Francisco, California. First, using quantitative data from electronic health records, we will conduct an interrupted time series analysis to quantitatively examine the impacts of the SCRT on people experiencing homelessness who utilized public behavioral health crisis services in San Francisco between November 2019 and August 2022, across four main outcomes within 30 days of the crisis episode: routine care utilization, crisis care reutilization, assessment for housing services, and jail entry. Second, to understand its impact on health equity, we will analyze racial and ethnic disparities in these outcomes prior to and after implementation of the SCRT. For the qualitative component, we will conduct semi-structured interviews with recipients of the SCRT’s services to understand their experiences of the intervention and to identify how the SCRT influenced their health-related trajectories after the crisis encounter. Once complete, the quantitative and qualitative findings will be further analyzed in tandem to assist with more nuanced understanding of the effectiveness of the SCRT program. This evaluation of a novel mobile crisis response program will advance the field, while also providing a model for how real-world program implementation can be achieved in crisis service settings.

## Introduction

Mobile crisis services for people experiencing distress related to mental health or substance use are expanding rapidly across the US [1]. Mobile crisis has a unique ability to respond rapidly in a less restrictive environment [2] and to coordinate with community partners such as law enforcement and emergency departments to divert people from those settings [3]. Recent federal legislation incentivized Medicaid coverage for mobile crisis services, and state and local governments have begun to invest significantly in expanding these programs [4].

With suicide rates and overdose deaths continuing to climb [5, 6], scarce resources and strained workforce must be positioned to be as high impact as possible. Although clinical trials in crisis services are often unfeasible given the high acuity of clinical scenarios and limitations to ethical randomization to experimental conditions, the creation of a range of crisis programs in real-world settings presents an opportunity to use implementation science methods to characterize which programs and models are meeting their stated objectives and informing future best practices [7].

Prior single-site quasi-experimental studies of mobile crisis programs have found impacts on service utilization and costs [8]. However, there are many remaining questions about how effective mobile crisis teams are at linking people to routine care and social services or at preventing adverse outcomes such as jail entry or reutilization of acute care services. Furthermore, while mobile crisis programs are often justified by reducing criminalization of people with mental illness, few studies have focused on programs that target high-risk populations such as people experiencing homelessness (PEH) [9, 10].

This paper describes the research protocol for an evaluation of a Street Crisis Response Team (SCRT) in San Francisco, California, a model that tailors its services to PEH. Mental illness and substance use disorders are highly prevalent among adult PEH in San Francisco, yet access to appropriately tailored services is limited. Especially troubling is the inequity of the burden of these diagnoses within this population: a third of PEH in San Francisco identify as Black/African American, compared to 5% of the overall population. Across the US, people with serious mental illness comprise approximately one quarter of all PEH, and up to one third has a substance use disorder [2], with people of color dramatically over-represented in this population [11]. Despite these trends, engaging PEH in mental health and substance use care as well as social services is impeded by marginalization, dehumanization, and structural violence, which interfere with trust and engagement in health care and social services [12].

We will employ an implementation science approach to study a novel mobile crisis program by drawing on empirical data from the health care system as well as perspectives from service recipients, which will allow for a deeper understanding of the utility—and potential limitations—of measuring traditional service outcomes in this setting [13]. We anticipate that this study will yield findings that inform both the implementation of existing, and the planning and evaluation of future mobile crisis programs.

## Methods

To evaluate the impact of the SCRT, we will use a QUANT-QUAL mixed methods implementation science approach [14, 15]. First, we will use quantitative methods to examine if there are changes in utilization of mental health, substance use, and housing services as well as jail entry following implementation of the SCRT among PEH who present in behavioral health crisis to acute care settings within San Francisco’s public health system. Second, we will evaluate the ability of the SCRT to enhance equity by stratifying our analysis by ethnoracial groups to examine pre-implementation disparities as well as post-implementation worsening, perpetuation, or resolution of baseline disparities. We will use our quantitative analysis to set the sampling frame for qualitative semi-structured interviews, which will be conducted with the SCRT service recipients to understand the facilitators and barriers to achieving their goals. Finally, we will consider the quantitative and qualitative results in combination to help interpret both sets of findings.

Study procedures were approved by the University of California, San Francisco, Committee on Human Subjects Research (Protocol #20–32693). The Committee waived consent for review of healthcare, housing, and jail records, and approved verbal informed consent procedures for telephonic and in-person interview participants.

### Program

The Behavioral Health Services division of the San Francisco Department of Public Health (SFDPH) has an extensive infrastructure for mental health and substance use disorder services, yet one important gap has remained: real-time response for people in behavioral health crisis in the streets. In 2019, San Francisco’s 9-1-1 call data indicates that approximately 50,000 behavioral health related calls were received, most of which were responded to by a law enforcement unit. Because most calls were not related to criminal events, and instead to mental health and social needs experienced by PEH, San Francisco behavioral health and governmental leaders worked with community stakeholders to create the SCRT to respond as an alternative able to be more responsive to behavioral health crises that happen on the street [16].

The SCRT was designed based on previous co-responder models [17, 18]. To meet the goal of diverting calls that would typically go to the San Francisco Police Department, this trauma-informed specialty behavioral health team is dispatched solely by 9-1-1 operators. The SCRT utilizes a co-responder model comprised of a behavioral health clinician, a paramedic from the San Francisco Fire Department and a peer specialist. Each team member plays a role in providing care including immediate stabilization of urgent medical need (paramedic), de-escalation of the crisis (behavioral health clinician) and person-centered peer support (peer specialist). The team triages clients to the appropriate level of care, be it through resolution of the crisis in the field, linkage to outpatient mental health and substance use services, or transport to an acute treatment setting. The SCRT was first piloted in San Francisco’s highest demand neighborhoods in December 2020 and then was incrementally expanded to be citywide by June 2021 (Fig 1).

**Fig 1 pone.0295178.g001:**
[figure not shown]
Rollout of the street crisis response team across San Francisco by region, hours of operation, and launch date of each phase of expansion. Landsat-7 image courtesy of the U.S. Geological Survey.

The SCRT also includes follow-up services provided by the Office of Coordinated Care (OCC), which is charged with offering support after the SCRT encounter with the goal of linking clients to outpatient mental health and housing services, thus reducing reutilization of acute services.

### Quantitative methods

To assess the implementation of the SCRT, we will use an interrupted time series (ITS) design, which is a quasi-experimental method that allows for non-randomized evaluation of an intervention [19]. In this ITS study, we will measure the effect of the intervention by generating models to assess changes over time in each outcome before and after implementation of the SCRT. This will allow us to model the secular trends in data not due to the intervention itself.

#### Study population

The SCRT aims to provide specialty mental health response and enhanced resources to adults in San Francisco who experience crises related to mental health and/or substance use disorders and are experiencing homelessness. Therefore, the study population will be defined based on age greater than 18 years, meeting criteria for homelessness in the 12 months prior to or 3 months following the crisis episode, and receipt of crisis care from any of San Francisco’s “front door” programs for people in an acute behavioral health crisis. These settings include two mobile crisis programs (Comprehensive Crisis Services and the SCRT), a crisis stabilization unit (DORE Urgent Care Clinic), and emergency psychiatric services (Zuckerberg San Francisco General Hospital’s Psychiatric Emergency Services [PES] and Emergency Department visits with a primary behavioral health diagnosis) (Fig 2). The population of housed adults utilizing acute behavioral health services will be utilized as a control group in the ITS sensitivity analyses.

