#### Data sources and matching procedures

The primary data sources for our quantitative analysis will include electronic health record (EHR) data from the network of clinics funded by the city’s health plan, public housing assessment data, and jail entry data. We will integrate data from SFDPH’s two main EHR vendors, Avatar (NetSmart) and EPIC, which are used by SFDPH mental health and substance use treatment providers, medical clinics, mobile crisis teams, crisis stabilization units, and Zuckerberg San Francisco General Hospital’s medical ED, psychiatric emergency services (PES) and inpatient psychiatry. Homelessness and housing assessment data originate from the Homeless Management Information System (HMIS), which is used by all entry points into the housing service system in San Francisco and automatically links data into the EPIC EHR. Jail entry data originates from the Jail Information Management System (JIMS), which the Department of Public Health’s Jail Health Services clinicians use to assess every person who enters the San Francisco County Jail, as well as Epic following their transition to this EHR in October 2021.

We will use a two-step process for linking records from the Avatar, Epic (including HMIS) and JIMS EHRs by first matching on demographic data fields such as first and last name, date of birth, legal sex, and at least one additional element (e.g., Social Security Number (SSN), full street address, phone number, or email address), and then an additional round of name matching using a Jaro-Winkler based process with matching parameter = 1 (i.e., exact match) [20, 21]. Unique individuals and episodes will be assigned anonymized identifiers to create a limited dataset that includes information about demographics, clinical attributes, dates of service, and zip codes. Authors did not have access to personal health information or other personal data that could identify individuals during or after data collection for the ITS.

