#### Index crisis episode

Conducting an ITS that includes a time-dependent outcome—in this case a routine care episode, acute care episode, housing assessment, or jail entry within 30 days following a crisis episode—requires defining an index crisis episode to start the clock for the outcome time interval. Furthermore, given that there may be multiple index episodes per unique individual, the index crisis episode needs to be defined per ITS interval, which, based on our preliminary power analysis, will be divided as one calendar month per interval. The index crisis episode will therefore be defined as the first instance in a given month that an individual has a crisis episode, with the 30-day post-crisis outcome period trailing the end date of the index episode.

We also need to account for the fact that a single crisis episode may result in multiple contacts with different settings in the acute behavioral health care system. To account for this variability, we will use our clinical knowledge of common care pathways as the basis for a crisis system map (Fig 2) that defines different sequences of care as either a step-up in service intensity (e.g., mobile crisis followed by crisis stabilization or ED), a step-down in service intensity (e.g., PES followed by crisis stabilization), or a distinct crisis episode that mostly likely signifies reutilization (e.g., PES followed by mobile crisis, or two consecutive mobile crisis episodes). We will then combine sequences with a step up or down in service intensity that occur within two or fewer days between the end of the first and start of the second clinical setting, so as not to miscount these care transitions as reutilization. This approach also allows us to create a variable describing these crisis system trajectories, thus allowing us to identify potential differences between index crisis episodes based on crisis system entry point and end point. All crisis services utilized three or more days after the index crisis episode end date will be considered separate from the index crisis episode.

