#### Outcome variables

We will build ITS models using the following four repeated measures outcomes: 1) post-crisis episode routine care utilization within 30 days; 2) post-crisis episode crisis service reutilization within 30 days; 3) post-crisis episode housing assessment within 30 days; and 4) post-crisis episode jail entry within 30 days. Routine care services will include receipt of outpatient services within 30-days following the index crisis episode in programs related to mental health, substance use, primary care, and integrated behavioral health in primary care. We will exclude residential programs and other services that are not intended to serve as routine care nor as a front-door crisis service. Acute care reutilization will include when an individual has a crisis care episode within 30-days following discharge from the index crisis episode. Housing assessment will be determined among those who are identified as PEH as having an HMIS record of receiving a housing assessment within 30-days following the index crisis episode. Finally, we will measure jail entry within 30-days following the index crisis episode based on clinical records from JIMS or Epic that are documented for every person who enters the San Francisco County Jail.

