#### Covariates

Demographic variables for age at time of service, gender identity, sexual orientation, race/ethnicity, housing status and insurance status will be developed in accordance with existing SFDPH reporting guidelines. Gender identity will be determined by information on each person’s sex at birth as well as self-reported gender identity to create categories for cisgender male or female, transgender male or female, and genderqueer or nonbinary. Sexual orientation is based on self-report. Race and ethnicity are recorded separately in both EHR systems and will be cross-referenced and then combined into a single variable by replacing race with ethnicity for those who identify as Hispanic/Latinx [22]. SFDPH defines someone as a person experiencing homelessness if they utilize a service that indicates housing instability (e.g., emergency shelter) or self-report homelessness while accessing health care services. Insurance status at the time of an encounter will be based on EHR billing records and grouped into descriptive categories (e.g., private versus public insurance). A location variable using zip code will be based on last location documented prior to the crisis episode. Multiple imputation will be used to account for missing data.

Diagnoses associated with service encounters will be categorized using the primary ICD-10 diagnostic code based on the Health Care Utilization Project’s Clinical Classifications Software Refined (CCSR) [23]. Given the unreliability of diagnosis data at the time of a crisis encounter [24, 25], we will use diagnoses made in routine service settings in the 90 days prior to the index crisis episode and, only if routine care is unavailable, will use acute-care settings diagnoses.

Additional clinical variables will include whether the index crisis episode resulted in an involuntary psychiatric hold; suicidality as part of the presentation (based on ICD-10 Z codes as well as clinical documentation or indication for involuntary holds as “danger to self”); and violence risk (based on clinical documentation or indication for involuntary holds as “danger to others”) [26]. We will also control for continuous variables describing the number of crisis services, routine care, jail, or housing assessment encounters in the 12-months prior to the index crisis episode. We will also assess the number of crisis services, routine care, jail, or housing assessment encounters in the 12-months prior to the index crisis episode.

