This analysis will use several design and analysis strategies to account for potential threats to internal validity. First, the study design using two nonequivalent groups with staggered implementation (crisis episodes with zip codes corresponding to neighborhoods that did or did not have the SCRT active during the partial implementation phase prior to citywide expansion) will allow for a between-site comparison of the pilot catchment area relative to the non-pilot areas (Fig 1). Additional sub-analyses will examine within-site differences for the pilot neighborhoods across the three time periods, and, separately, within-site differences for the non-pilot neighborhoods. Second, a non-equivalent non-treatment control group (non-homeless adults accessing crisis services) will be compared to the target population (homeless adults accessing crisis services) using a difference of differences approach to account for secular variations in mental health and substance use service utilization. Third, a series of non-equivalent dependent outcome variables that are not expected to be impacted by the implementation of the SCRT (e.g., non-crisis initiation of outpatient mental health services) will be evaluated across the same time periods with a similar goal of accounting for secular variations in mental health service utilization. Additional issues such as autocorrelation of repeated measures on individuals will be corrected for in the final analyses.

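### Homelessness status may be set by contacts up to 3 months after the crisis, a window that contains the 30-day outcomes, so post-crisis contact can decide who is in the denominator

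*Protocol article*

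**What the plan says.** Five parts of the protocol article bear on this.

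- **Eligibility (Study population).** A person belongs to the target population by "meeting criteria for homelessness in the 12 months prior to or 3 months following the crisis episode".
- **What counts as homeless (Covariates).** A person is classed as homeless "if they utilize a service that indicates housing instability (e.g., emergency shelter) or self-report homelessness while accessing health care services". Both routes need a contact with a service.
- **Data source (Data sources and matching procedures).** "Homelessness and housing assessment data originate from the Homeless Management Information System (HMIS"), a system "which is used by all entry points into the housing service system in San Francisco".
- **Outcomes (Index crisis episode; Outcome variables).** All four outcomes use a 30-day clock, "with the 30-day post-crisis outcome period trailing the end date of the index episode". For housing, "Housing assessment will be determined among those who are identified as PEH as having an HMIS record of receiving a housing assessment within 30-days".
- **Intervention (Program, last paragraph).** SCRT includes follow-up by the Office of Coordinated Care "with the goal of linking clients to outpatient mental health and housing services".

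The Interrupted time series analysis section divides each monthly count by the whole target population of that month. It also plans a difference-in-differences comparison with housed adults, which Study population places among the sensitivity analyses. Nothing in the article limits the primary analysis to homelessness recorded before or at the crisis, or tests the look-ahead. The Limitations section does not mention it.

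**The concern.** Eligibility should be settled by what is known when the outcome clock starts. Here it can be settled by what happens while the clock is running. Take an adult with no homelessness record in the previous 12 months. If a contact in the next 3 months leads to a record of homelessness, that person joins the target population, together with any outcome that occurred at or through the contact. Without such a contact the person is not in the target population at all. This is selection on information that arises after exposure.

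A time-series design removes a distortion that is the same in every period. It does not remove one that changes at the interruption, and the article itself gives a reason to expect change: follow-up aimed at housing and outpatient linkage is part of the intervention. What is at stake is whether a change in the monthly proportion reflects what SCRT did for a fixed kind of patient, or a change in who was recorded as homeless.

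**Working it through.** **Step 1: compare the windows.** Eligibility runs from 12 months before the crisis to 3 months after it. Outcomes run for 30 days after the end of the index episode. The outcome period therefore falls in the first part of the look-ahead.

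**Step 2: ask which outcomes can also set the flag.**
- *Housing assessment.* Flag and outcome data share one system, and an assessment is a contact with the housing service system. It is reasonable to infer that it can set the flag, but the article gives only emergency shelter as its example.
- *Routine care.* An outpatient visit is an occasion to self-report homelessness while accessing health care, so this route follows from the stated definition.
- *Crisis reutilization and jail entry.* Self-report at those contacts is possible. The article does not say that jail contact is used this way.

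**Step 3: illustrate the mechanism.** The article gives no sample size, rate or count, so there is no figure to reproduce and every input here is assumed. Per 1,000 truly homeless adults in crisis care, let

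- F = number flagged before the crisis, and M = number not flagged before, with F + M = 1,000;
- p = true 30-day housing-assessment risk, the same in both groups;
- q = chance that a person without the outcome is flagged by some other contact within 3 months;
- the outcome always flags the person (the inferred link).

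Observed proportion = (F·p + M·p) / (F + M·[p + (1 − p)·q])

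With p = 10% the numerator is always 100:

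| M | q | Denominator | Observed |
|---|---|---|---|
| 200 | 0.3 | 800 + 200 × 0.37 = 874 | 11.4% |
| 400 | 0.3 | 600 + 400 × 0.37 = 748 | 13.4% |
| 200 | 0.8 | 800 + 200 × 0.82 = 964 | 10.4% |
| 400 | 0.8 | 600 + 400 × 0.82 = 928 | 10.8% |
| any | 1 | 1,000 | 10.0% |

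Over M = 100 to 400 and q = 0 to 1, the observed level is 5.0% to 8.1% when p = 5%, 10.0% to 15.6% when p = 10%, and 20.0% to 29.4% when p = 20%.

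**Step 4: pre-post change with no true effect (p = 10% throughout).**
- M and q constant: 0.0 points.
- M rises from 200 to 400, q = 0.3: 13.37 − 11.44 = +1.9 points.
- q rises from 0.3 to 0.8, M = 200: 10.37 − 11.44 = −1.1 points.
- q rises from 0.3 to 0.8, M = 400: 10.78 − 13.37 = −2.6 points.
- Both rise (M from 200 to 400, q from 0.3 to 0.8): 10.78 − 11.44 = −0.7 points.

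The sign depends on what changes. If more people without an earlier record enter crisis care, the proportion is pushed up. If follow-up flags more people who lack the outcome, it is pushed down.

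**Step 5: the housed comparison.** The control, described as a "non-equivalent non-treatment control group (non-homeless adults accessing crisis services"), is the complement of the same flag. For routine care, someone newly flagged at a visit leaves the control and enters the target with that visit counted. The comparison therefore shares the misclassification for outcomes measured in both groups. Housing assessment is not one of them, because it is determined only among people identified as homeless.

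**Step 6: under the fix.** With status fixed at the end of the index episode, the illustration returns p, and the spurious change is 0 whatever M and q are. This relies on p being the same in flagged and unflagged people.

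**The case against.** A reader might infer that the rule manufactures an SCRT benefit on housing assessment. The documents do not support that.

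- **Extra assessments may be real.** Suppose 800 people are already flagged with 10% assessed, newly flagged people rise from 60 to 120 per month, and half of them were flagged through an assessment. The measured rate goes from (80 + 30)/860 = 12.8% to (80 + 60)/920 = 15.2%, or +2.4 points. But if SCRT caused the 30 extra assessments, they are effect and not artefact. With a constant pool of 300 unflagged homeless adults, the true rate goes from 110/1,100 = 10.0% to 140/1,100 = 12.7%, or +2.7 points. Pools of 120 to 600 give true changes of +3.3 to +2.1 points. Counts like these cannot separate the two.
- **The direction is open.** It can be zero or negative, as Step 4 shows.
- **The link from assessment to flag is inferred.** One data system holding both items does not prove that one sets the other.
- **The housed control loses no housing successes,** because the outcome is not measured there.
- **Reach is limited.** Only people with no flag in the previous 12 months are affected, and their share is not given. Models also adjust for service counts in the prior 12 months.
- **The look-ahead has a purpose.** It may recover homelessness that was under-recorded at the crisis.

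All of this stands as a limit on size and sign. It does not remove the defect. Covariate adjustment cannot bring back people who never entered the target population, and recovering missed cases can be done in a sensitivity analysis.

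**Conclusion.** The point holds in limited form. The article states a rule under which homelessness recorded after the crisis, during the outcome period and beyond, decides membership of the target population, and nothing shown restricts or tests it. If this ascertainment changes with SCRT rollout, the pre-post change can be biased either way, most directly for housing assessment and also for routine care. If ascertainment is constant, only the level is distorted.

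The size cannot be determined from the document. The range of −2.6 to +1.9 points is illustrative. It rests on an assumed 10% risk, 200 to 400 previously unflagged people per 1,000, other-contact flagging of 30% to 80%, and the inference that an assessment sets the flag. The last of these is not needed for routine care, where self-report during a health care contact is enough. The change is a cheap improvement; the document does not show that the planned results would be wrong.

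**What to change.** 1. In the primary analysis, define homelessness from information dated in the 12 months before the index episode up to its end date, and hold that status for the episode.
2. Keep the 3-month look-ahead as a labelled sensitivity analysis.
3. Report, by month and by period, how many people qualify only through the look-ahead. A stable count and share would be reassuring; a step at rollout would be a warning.
4. Exclude those people from the housed control. Reclassifying them as housed would put homeless people, some of them exposed to SCRT, into the comparison group.

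Cost: one eligibility sentence and a flag re-derived by date from records already being linked. The primary sample becomes smaller, by an amount the article does not allow one to estimate, and omits homeless people with no earlier record. Flags recorded at the index encounter still count, so ascertainment may still vary with rollout. The change removes selection on later events, not every difference in recording.
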